## Abstract

**Background:**

Well-organised and managed workplaces can be a source of wellbeing. The construction, healthcare and information and communication technology sectors are characterised by work-related stressors (e.g. high workloads, tight deadlines) which are associated with poorer mental health and wellbeing. The MENTUPP intervention is a flexibly delivered, multi-level approach to supporting small- and medium-sized enterprises (SMEs) in creating mentally healthy workplaces. The online intervention is tailored to each sector and designed to support employees and leaders dealing with mental health difficulties (e.g. stress), clinical level anxiety and depression, and combatting mental health-related stigma. This paper presents the protocol for the cluster randomised controlled trial (cRCT) of the MENTUPP intervention in eight European countries and Australia.

**Methods:**

Each intervention country will aim to recruit at least two SMEs in each of the three sectors. The design of the cRCT is based on the experiences of a pilot study and guided by a Theory of Change process that describes how the intervention is assumed to work. SMEs will be randomly assigned to the intervention or control conditions. The aim of the cRCT is to assess whether the MENTUPP intervention is effective in improving mental health and wellbeing (primary outcome) and reducing stigma, depression and suicidal behaviour (secondary outcome) in employees. The study will also involve a process and economic evaluation.

**Conclusions:**

At present, there is no known multi-level, tailored, flexible and accessible workplace-based intervention for the prevention of non-clinical and clinical symptoms of depression, anxiety and burnout, and the promotion of mental wellbeing. The results of this study will provide a comprehensive overview of the implementation and effectiveness of such an intervention in a variety of contexts, languages and cultures leading to the overall goal of delivering an evidence-based intervention for mental health in the workplace.

**Trial registration:**

Please refer to Item 2a and registration ISRCTN14104664. Registered on 12th July 2022.

**Supplementary Information:**

The online version contains supplementary material available at 10.1186/s13063-023-07537-0.

## Background

Mental health difficulties and disorders in the workplace severely impact businesses through absenteeism/presenteeism, decreased productivity, workplace accidents and even self-harm and suicide [1]. Employees in some sectors may be more at risk of experiencing mental health difficulties (e.g. burnout) or disorders, such as depression and anxiety. Male-dominated workplaces, such as the construction and ICT sectors, are characterised by high levels of mental health-related stigma and low levels of help-seeking for mental health concerns, despite increased psychological distress [2]. Paradoxically, stigmatising attitudes are common in healthcare professionals, which can have a negative impact on self-care behaviours [3]. These sectors have also been associated with an increased risk of suicide among workers [4], with male construction workers in the UK being almost four times more likely to die by suicide than the general working population [5].

Certain workplace-related factors may contribute to the development, exacerbation and maintenance of mental health difficulties. For example, an association with the risk for depressive disorders has been found for the combination of high demands and low control [6], for the imbalance between high efforts and low rewards [7] and for workplace bullying [8], making the workplace an important setting for interventions. Organisation size is another factor which may contribute to employee wellbeing. Small- to medium-sized enterprises (SMEs) are the most common form of workplace in the European Union and they employ a significantly larger share of employees compared to larger organisations [9]. Research indicates that SMEs face additional workplace stressors, such as social isolation, long work hours, out-dated technologies, lack of human resource management systems, economic uncertainty and financial pressures [10, 11]. These are exacerbated by a lack of infrastructure to develop expertise, knowledge and resources to invest in workplace occupational health programmes [12–14]. Although SMEs may not usually have the financial resources to address employee mental health, they may be in a unique position to promote mental health, prevent clinical and non-clinical mental health difficulties and reduce mental health-related stigma. The COVID-19 pandemic has further exacerbated risk factors contributing to mental health difficulties while greatly reducing social interactions and opportunities for support from colleagues. It is anticipated that the long-lasting impacts of the pandemic may include increased levels of depression, self-harm and suicidality [15–17] as well as anxiety, post-traumatic stress disorder and sleep disorders, which may be compounded by job insecurity and long periods of isolation associated with the pandemic [18]. Europe, in particular, now is faced with a new economic crisis, caused by the war in Ukraine and the rapid increase in energy prices that are also placing great financial worries on both business and the general public.

According to a systematic meta-review, there is moderate evidence that workplace factors such as high job demands, low job control, role stress, bullying and low social support can be associated with a heightened risk for the onset of negative mental health outcomes [19]. Workplaces that intervene to offset these factors are more likely to reduce negative mental health outcomes, as well as absenteeism and presenteeism, and ultimately, may increase productivity and contribute to economic gains [11, 20–22]. Research in the construction sector has shown that the implementation of an occupational intervention for minor depressive symptoms may prevent more serious depressive symptoms, including suicidal thoughts and behaviours [23, 24]. Furthermore, some evidence suggests educational interventions in the healthcare sector are effective in decreasing mental health-related stigma [3, 25].

The literature on workplace mental health interventions indicates that a multi-level approach which encompasses the organisational level and the individual level can be successful in reducing burnout [26–29], anxiety [30], stress [31, 32] and stigma [33]. A key factor in the multi-level approach is the active role that management needs to play in ensuring the intervention fits with existing policies and practices within the organisation as well as providing the resources for implementation [34, 35]. Management has the ability to directly influence workplace stressors through policy, work redesign or modification of work processes and support structures [36]. Another key factor is the implementation of components that directly target the individual within the organisation, thereby implementing a top-down (via management) and a bottom-up (via employees) approach [37]. Successful workplace mental health interventions also incorporate members of the workforce in their planning and delivery, reinforcing the value of both organisational and individual level buy-in [38].

In addition to a multi-level approach, interventions that are tailored to the needs of the specific workplace or sector have the potential to be more effective [39]. This includes presenting information using images and scenarios which the individual would find relatable and providing a variety of intervention components that workplaces can choose from to fit the intervention activities to their actual needs [40]. Accessible workplace interventions are also integral to effective implementation. In recent years, interventions delivered through digital technologies have been successful in engaging a wide range of users across the organisation [41] and in reducing stress [42] and mild depressive symptoms [43].

Well-organised and managed workplaces can be a source of wellbeing [44–46]. There has been an increase in workplaces interested in supporting their employees to prevent, detect and manage mental health difficulties and disorders in the workplace [14]. However, only 7% of mental health promotion and prevention programmes globally are workplace-based [47]. There is a need and demand for methodologically sound research studies to examine the efficacy of implementing mental health interventions designed for the workplace. At present, there is no known multi-level, tailored, flexible and accessible workplace-based mental health intervention targeting a spectrum of non-clinical and clinical symptoms. The EU Horizon 2020 project Mental Health Promotion and Intervention in Occupational Settings (MENTUPP) aims to fill this gap.

The MENTUPP workplace intervention targets clinical mental disorders (depression and anxiety disorders), non-clinical mental health problems (stress, burnout, depressive symptoms) and mental health stigma and supports positive mental wellbeing by adopting the multi-level approach. The MENTUPP intervention aims to protect mental health by promoting mental health in the workplace (primary prevention), reducing work-related risk factors (secondary prevention) and targeting mental health problems as they develop (tertiary prevention) [48] by providing guidance and support for all employees and management in the organisation. The MENTUPP approach adopts several theoretical frameworks including the Integrated Mental Health Framework by LaMontagne and colleagues [49] which includes three threads: (i) Protect mental health by controlling harmful work exposures; (ii) promote mental health by building on strengths and (iii) address mental health problems regardless of cause. Furthermore, it uses the Dual Mental Dual Continuum Wellbeing Framework by Keyes to differentiate between mental health and mental wellbeing [50]. The materials developed for the MENTUPP intervention are tailored to three at-risk sectors: construction, healthcare and information and communication technology (ICT) to enhance the uptake and potential effectiveness [51] and are available online through the MENTUPP Hub. Digital interventions are appropriate for increasing reach [52], particularly in the context of sectors that have inflexible shift patterns (i.e. healthcare, ICT), that have employees working on various sites (i.e. construction) or employees working remotely (ICT).

The overall goal of the MENTUPP intervention is to improve mental health and mental wellbeing in the workplace, with secondary aims of reducing stigma, depression and suicidal behaviour by providing tailored mental health promotion materials for the construction, healthcare and ICT sectors. MENTUPP provides SMEs with easily accessible tools for leaders and for employees that make it possible to address mental health issues on the workplace-level and the employee level.

## Objectives

Based on the results and experiences of a pilot study [53, 54], the present paper outlines the protocol for the cluster Randomised Controlled Trial (cRCT) which will investigate the effectiveness of the intervention in improving mental health and wellbeing (primary outcome) and reducing stigma, depression and suicidal behaviour (secondary outcome) in employees. Furthermore, multi-level workplace interventions always interact within context and can not only be assessed for their effects on mental health outcomes, but need to also have a sufficient process evaluation in order to investigate the mechanisms of effectiveness [55]. Given that resources are limited it is also insufficient just to look at the effectiveness of interventions, it is important to also consider their relative cost-effectiveness. This is particularly important in the case of SME’s which can be operating under conditions of substantial financial uncertainty. Therefore, the study will also involve a process and economic evaluation. In this article, we will present the protocol for the cRCT of the MENTUPP intervention in eight European countries and Australia.

## Methods/design

The manuscript has been developed in line with the SPIRIT reporting guidelines [56].

### Study design

A cRCT will be conducted with SMEs in two conditions, intervention and control, within each of the three sectors: healthcare, construction and ICT. Quantitative and qualitative evaluation data will be obtained and guided by the RE-AIM framework [57] and the evaluation framework of Proctor et al. [58], to structure the outcome, process and economic evaluation of the MENTUPP intervention from data collected at baseline, 6-month and 9-month follow-ups. Five types of evaluation measures will be collected: six validated questionnaires, two self-developed surveys, a monitoring instrument and user data from the MENTUPP Hub. Focus groups conducted with the local research officers post-intervention will inform process evaluation and how the Hub was implemented locally. The intervention group will complete the baseline survey and receive immediate access to the MENTUPP Hub. They will also complete the 6-month and 9-month follow-up measures. The control group will complete the baseline, 6-month and 9-month measures. Following the completion of the 9-month measures, participants of the control group will receive access to the MENTUPP Hub (see Fig. 1 for timeline).

**Fig. 1 Fig1:**

MENTUPP cRCT timeline

### Study population

#### Organisations

Organisations that fit the criteria of being an SME will be invited to participate in the study. SMEs are defined as organisations with fewer than 250 employees [9]. A small sized enterprise is defined as an organisation with fewer than 50 employees and a medium-sized enterprise consists of 50–249 employees. Definitions and inclusion criteria of the SMEs in the construction, healthcare and ICT sectors are based on Nomenclature of Economic Activities (NACE) guidelines [59]. The aim is to recruit a minimum of two SMEs from each of the three targeted sectors, construction, healthcare and ICT, across the nine participating countries: Australia, Albania, Ireland, Netherlands, Hungary, Kosovo, Germany, Finland and Spain. If significant issues arise with the recruitment of SMEs as per the strict criteria, consideration will be given to broaden the definition to include slightly larger organisations (e.g. 300 employees).

### Participants

Individuals will be eligible to participate in the MENTUPP intervention if they are (1) full- or part-time employees, including contractors, supervisors and individuals on sick leave or other types of authorised leave (e.g. maternity or care leave); (2) employed within an eligible SME in the construction, healthcare or ICT sector; (3) aged 18 years or older; and (4) willing to give their informed consent for participation. Any individual within an organisation who has any type of managerial or leadership role will be referred to as ‘leader’ in the MENTUPP project.

### Sample size

In each of the nine countries, local research officers will use convenience sampling to recruit a minimum of two SMEs in each of the three sectors, yielding a total of at least 54 participating SMEs, half for intervention and half for control. An average of 65 participants per SME will be recruited at baseline. Allowing for an estimated attrition rate of 65%, based on the pilot study and previous literature [60, 61], this will yield baseline and follow-up data for 23 participants per SME. A sample size of 621 participants (i.e. 27 SMEs with 23 participants) in each arm of the cRCT achieves 85% power to detect a difference of 0.25 standard deviations between the mean change in intervention participants and the mean change in control participants, when the intra-cluster correlation is 0.05, using a two-sided independent *t*-test with a significance level of 0.05.

### Description of the study intervention

#### Materials

The MENTUPP intervention has been developed and designed to improve mental health and wellbeing and reduce stigma in the workplace and is facilitated through the MENTUPP Hub, an online platform that presents interactive psychoeducational materials, toolkits and links to additional resources (See Fig. 2—screenshot of Hub).

**Fig. 2 Fig2:**
[figure not shown]
Screenshot of MENTUPP Hub springboard page which links to modules

All online intervention materials designed and developed for the MENTUPP Hub were optimised following a pilot study in relation to the key messages, content, visuals and the structure [53]. The optimisation process was informed by a series of systematic reviews on the implementation of mental health promotion interventions in workplace settings and on psychosocial interventions for depression, anxiety and suicidal ideation and behaviours in SMEs [62–64], recommendations from local research officers received during the pilot study, the results of the evaluation measures and focus groups from the pilot study, and feedback from local Steering Groups comprised of representatives from each of the sectors. The main changes to the online intervention materials were informed by a synthesis of the collated documents to produce a more engaging, coherent, user-friendly experience with simple language and improved structure and navigation throughout the online platform (see Figs. 2 and 3).

**Fig. 3 Fig3:**
[figure not shown]
Screenshot of module links within MENTUPP Hub

The optimised MENTUPP Hub is comprised of eight modules with tailored visuals, videos and case study content within each sector, which are also tailored to different organisations levels. MENTUPP is a multi-level intervention designed to target all levels of the organisation; the employees, management and the organisation as a whole. Furthermore, materials are tailored for each sector to ensure that the language and content of materials is relevant to the construction, healthcare and ICT sectors. The interactive materials are delivered through online information packages, videos, pre-recorded roleplays, animated scenarios of case studies, short quizzes, reflection exercises, breathing and mindfulness exercises and practical stress management exercises [53].

### Languages

All materials in the MENTUPP Hub and the associated evaluation will be available in the national languages spoken in the intervention countries: Albanian, Dutch, English, Finnish, German, Hungarian and Spanish. Three additional languages, Polish, Turkish and Ukrainian, that are frequently spoken among employees in the recruited SMEs determined by the pilot and local steering groups, will also be available. The language of the informed consent and registration process is dictated by the country location of initial access. Following informed consent and registration, participants may select their preferred language to engage with the MENTUPP Hub.

### Procedure

#### SME recruitment

The standard operating procedures utilised in the pilot study will also be used to guide the recruitment and initial interaction and engagement with SMEs for the local research officers to assess eligibility, participation and commitment [53]. In addition to seeking guidance on recruitment of SMEs from local steering groups, SMEs who participated in the pilot study will also be contacted for snowball recruitment.

### Randomisation of SMEs

Local research officers will assign a pseudonym to each participating SME. SMEs will be allocated to either the intervention or control conditions using block randomisation. This will be completed by the evaluation team, who remain blinded to the identity of the SMEs. To maintain balance between the intervention and control groups, group allocation will be conducted in pairs of SMEs within each sector in each country. This process will be repeated to create a list of SMEs with group allocation. Minimisation is expected to be used when an unpaired SME is required to be allocated to a condition [65]. The first SME will be allocated to the intervention or control group at random. The allocation status of the subsequent SME will be determined based on the allocation of the first SME in a manner that would lead to better balance between the groups in the variables of interest.

After randomisation is complete, the local research officers will contact each SME to inform them of their randomisation status. The meeting will involve discussing the appointment of the designated communications person within the SME, the purpose of the surveys and what is involved in them and clarifying the details of implementing and scheduling the introductory sessions within the SME. Participants and the local research officer will not be blinded to allocation status; however, analysts evaluating the outcome will be blinded.

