### Individual recruitment

In partnership with the SME, the local research officers will conduct introductory sessions with the employees including a short presentation describing the purpose of the research. The local research officers will emphasise that participation is voluntary, and employers will not be notified about who is participating within their organisation. Participants will also be informed that they can withdraw from the research at any time without repercussions. Participants will also be given the opportunity to ask any questions they may have. The research officer will provide information on who to contact and how to contact them for any support or assistance. All employees will receive a link to the information sheet and an informed consent form.

For the intervention group, the local research officer will also explain the registration process for access to the MENTUPP Hub and what materials are available on the Hub. For the control group, the local research officer will explain that they will be given access to the MENTUPP Hub at the end of the study period.

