## Data management

Qualtrics [76], a General Data Protection Regulation (GDPR) compliant online platform, will be used to collect data from the validated questionnaires and the two self-developed surveys. To allow matching of the data collected of the same subject at multiple timepoints, an anonymous subject-generated identification code (ID-code) will be used [77]. For participants within the control group, the Qualtrics links will be distributed by email from the local research officers. Participants will be asked to answer four neutral questions at the first of the three time points of data collection to generate an anonymous unique ID-code and ensure confidentiality. For participants in the intervention group, the Qualtrics links will be embedded in the registration process for the MENTUPP Hub. When registering for the MENTUPP Hub, participants will be asked to enter a self-chosen 4-digit code and the SME code.

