Some of the limitations associated with the study relate to the current challenging times, including the COVID-19 pandemic (particularly for the healthcare sector), increase in the cost of energy and the crisis in Ukraine (particularly for bordering European countries). These challenges may inhibit an organisation’s ability to opt into and adhere to the intervention and are outside the researchers’ control. However, the research team has attempted to alleviate these challenges by facilitating access to the intervention in a self-paced manner for workers to access in their own time, by presenting relatable material on the pandemic and tips on how to cope during the pandemic. The intervention has also been translated to the Ukrainian language to accommodate workers who may have been displaced due to the war.

The participation of SMEs and participants within SMEs is voluntary, which may cause self-selection bias to the study whereby SMEs and participants who already have an inherent interest in mental health may choose to participate. Self-selection bias into the study may limit the external validity of the study and limit the generalisability of results. However, very few research projects about mental health have been conducted in the construction industry. Therefore, even if the more interested workplaces select themselves into the study, it will be an improvement to document experiences from this sector which will help with future initiatives. Furthermore, the extensive process evaluation will nevertheless give us rich knowledge about these workplaces that will help to understand what is needed to also reach less motivated workplaces. Self-report measures employed to capture any potential change to mental health outcomes may also be influenced by response bias. As outlined above, the flexible approach to the trial may result in some variability in the reach and the implementation of the intervention in SMEs. However, this flexibility is an integral part of the study and considered a strength when applying interventions in real-life conditions.

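### Employees are enrolled and surveyed at baseline after their SME's allocation is disclosed, with an arm-specific message and survey entry, so randomisation protects comparability of SMEs but not of the employees who enrol

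*Protocol article*

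**What the plan says.** The order of events is set in the Protocol article, Randomisation of SMEs and Individual recruitment.

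- SMEs are randomised, and then "After randomisation is complete, the local research officers will contact each SME to inform them of their randomisation status".
- That same meeting includes "clarifying the details of implementing and scheduling the introductory sessions within the SME", so the employee sessions still lie ahead when the arm becomes known.
- On blinding: "Participants and the local research officer will not be blinded to allocation status; however, analysts evaluating the outcome will be blinded".
- The sessions are run by those officers: "In partnership with the SME, the local research officers will conduct introductory sessions with the employees". The consent step is described with them: "All employees will receive a link to the information sheet and an informed consent form".
- The message differs by arm. "For the intervention group, the local research officer will also explain the registration process for access to the MENTUPP Hub", together with what the Hub contains. Control employees are told that access comes at the end of the study.

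Survey entry also differs. Under Data management, "For participants in the intervention group, the Qualtrics links will be embedded in the registration process for the MENTUPP Hub", while control employees get the link by email from the research officer. Study design and Implementation add that the Hub is meant for people who have completed the baseline questionnaires and that intervention participants get access immediately. Controls get it after the 9-month measures.

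Under Missing data, intention-to-treat covers all participants by allocated group. The Discussion says of voluntary participation: "Self-selection bias into the study may limit the external validity of the study and limit the generalisability of results".

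**The concern.** In a cluster trial, randomising the clusters makes the clusters comparable. It makes the participants comparable only if they are identified and enrolled before allocation is known, or by a process that allocation cannot influence. Neither condition is met here. An employee deciding whether to take part knows whether the reward is immediate access to the Hub or a wait of at least nine months, and hears this from an officer who also knows. The people who say yes may therefore differ between arms in interest, need or readiness to change.

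The comparison at stake is the primary one and every other survey-based outcome. The economic evaluation draws on the same surveys. Increasing the sample does not reduce a bias of this kind.

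**Working it through.** **1. Sequence.** Set side by side, the sections give this order: randomise the SME; disclose the arm and schedule the sessions; hold the arm-specific sessions and send the consent link; take the baseline survey; open the Hub (intervention only). No sentence places employee listing, consent or baseline before disclosure, or uses a recruiter who does not know the arm. The timeline figure is not shown, but the prose alone fixes the order.

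**2. What differs by arm at enrolment.**

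| Element | Intervention | Control |
|---|---|---|
| Consent link | sent to all employees | sent to all employees |
| Session content | Hub registration and materials | access at end of study |
| Baseline survey link | inside Hub registration | emailed by research officer |
| Result of completing baseline | Hub opens at once | Hub after 9-month measures |

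**3. Do the stated safeguards reach this step?**

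- Pairing within sector and country, done by a team that does not know the SMEs' identity, acts on SMEs.
- Blinded analysts act after the data exist.
- Intention-to-treat starts from those who enrolled, so it inherits any imbalance in who enrolled.
- The mixed models (Data analysis, Outcome evaluation) use baseline. Adjustment reaches only measured differences, and here baseline is itself self-reported with the arm known.

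**4. The plan's own figure.** Inputs from Sample size: 27 SMEs × 23 = 621 per arm, ICC 0.05, difference 0.25 SD in mean change, two-sided 5%.

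- Design effect = 1 + (23 − 1) × 0.05 = 2.10
- Effective n per arm = 621 / 2.10 = 295.7
- SE of the difference = √(2 / 295.7) = 0.082 SD
- Power = 86.0% (normal approximation) or 84.7% (noncentral t, 52 df), against 85% stated. The stated power reproduces and is not in dispute.

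**5. Illustration of what a bias would do.** The document gives no bias figure, so the shift b is an assumption. It is expressed as a difference in mean *change*, the quantity on which the trial is powered. With no true effect, the rejection rate is 1 − Φ(1.96 − b/SE) + Φ(−1.96 − b/SE).

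| Assumed b (SD) | Rejection rate |
|---|---|
| 0 | 5% |
| 0.05 | 9% |
| 0.10 | 23% |
| 0.15 | 45% |
| 0.20 | 68% |

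Nothing in the document says which row applies, or that b is not zero.

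**The case against.** The strongest reply is that the design keeps a good deal of protection and that the harm is not shown. Much of this stands.

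- *A reader might infer that randomisation fails altogether.* It does not. SMEs are allocated in pairs within sector and country by a team that does not know which SME is which, so comparability of SMEs is preserved.
- *A reader might infer that consent itself is taken by two routes.* The consent link is described in the same terms for all employees. What differs is the session content, the survey entry and the timing of Hub access.
- *A reader might infer that nobody unwilling to register for the Hub can enter the intervention arm.* Data management points that way. However, the process-evaluation part of Data analysis says the log data can show which respondents registered, which suggests that some may not have. The text does not settle it.
- *A reader might attach a percentage of the target effect to the bias.* The trial is powered on a difference in mean change. Selection that shifts baseline and follow-up equally cancels in change, so a shift in outcome level cannot be set against 0.25 SD. The document supplies no uptake rates or correlations from which to work.
- *A reader might add other differences between arms.* The ID-codes are generated differently, but that concerns linkage over time and not who enrols. The items on expectations serve as adherence data in the intervention group, where knowing the arm is inherent. No differing route for the 6- and 9-month surveys is stated.

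The protocol is also open about the lack of blinding, acknowledges response bias, and promises controls later access, which narrows the gap in incentive. None of this moves enrolment ahead of disclosure.

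**Conclusion.** The point holds in a bounded form. Employees are approached, consented and given the baseline survey after their SME's arm is disclosed, by an unblinded officer whose message differs by arm, and they enter the survey by different routes with different immediate rewards. Comparability of SMEs is protected. Comparability of the enrolled employees is not, and the planned analysis cannot be relied on to restore it.

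This is a risk of bias, not a demonstrated one. Neither its size nor its direction follows from the document, and the rejection rates above rest wholly on assumed shifts. The conclusion assumes that the prose describes the actual order of conduct.

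The Discussion is wrong to confine self-selection to external validity. When the decision to enrol is made with the arm known, self-selection can differ by arm, and it then threatens internal validity.

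**What to change.** For SMEs not yet allocated or told their arm:

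1. Hold one introductory session with the same content whatever the allocation.
2. Collect consent and baseline through the same link in both arms, and close the SME's baseline window.
3. Only then disclose the allocation.
4. Make Hub registration a separate, later step for the intervention arm.
5. Define the primary analysis population as everyone who completed baseline before disclosure, whether or not they register for the Hub.

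For SMEs already allocated (the Economic evaluation section speaks of data collection in the present tense, so conduct may be under way): report the number of eligible employees and the number enrolled by SME and arm, compare baseline characteristics between arms, and state the limitation as one of internal validity. This makes the problem visible; it does not remove it.

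The cost is a change to the standard operating procedure and the survey set-up, with three downsides. There is a short wait before SMEs learn their arm. The extra registration step may lower Hub uptake, since the Discussion names registration as a significant barrier in the pilot. Employees who join after the baseline window fall outside the primary analysis, which matters most in construction, where the workforce is described as mobile.
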